## Abstract

**Objective:**

Sub-Saharan Africa has the highest prevalence of children at risk of not achieving their developmental potential, attributable largely to the human immunodeficiency virus (HIV) pandemic coupled with negative environmental factors. Childhood developmental stimulation programmes can mitigate adverse outcomes.

**Methods:**

Neonates testing HIV positive at birth will be initiated on antiretroviral treatment (ART) and receive an age-appropriate stimulation program, updated at 3 monthly intervals through the first year of life. Neurodevelopment at 12 months of age will be assessed using the Bayley Scales of Infant and Toddler Development, Third Edition (BSID-III). Outcomes will be compared with HIV-infected and HIV-exposed uninfected children (HEU) not having received the stimulatory intervention. Associations between neurodevelopmental outcomes, environmental factors, and parental stress will be investigated. The study will take place at a single site in Johannesburg, South Africa. This non-randomised controlled intervention study, with a single non-blinded comparative intervention group, aims to investigate whether an early childhood stimulation programme used in conjunction with ART initiated at birth can positively impact neurodevelopmental outcomes at 1 year of age in children infected with HIV.

*Trial registration* 15 January 2018, Pan African Clinical Trial Registry PACTR201801002967587

## Introduction

Worldwide an extraordinary number of children are at risk of not developing their full potential. Using poverty and stunting as proxy markers for estimating children at risk of early childhood developmental (ECD) delays, a 2010 Lancet Global Health report estimated that 249.4 million children (43% of all children in 2010) under the age of 5 years living in low- and middle-income countries (LMIC) were at risk of not reaching their developmental potential [1]. Sub-Saharan Africa was reported as having the highest prevalence of children at risk—66% in 2010. The HIV pandemic in South Africa contributes to this statistic with 240,000 (210,000–260,000) children under 15 years of age infected with HIV [2].

The human immunodeficiency virus is neurotropic and invasion of the developing infant brain results in significant negative neurodevelopmental consequences [3]. Reported developmental shortfalls include delays in motor, cognitive, and language development [4]. Careful assessment of the child’s developmental abilities is important as children may continue to acquire new skills, but function consistently below the age-related developmental norm on standardised assessments [5]. The severity of the neurological deficit is increased relative to the degree of immunosuppression, stage of HIV disease [6], and timing of ART initiation. ART started at a young age is associated with improved neurocognitive outcomes [7, 8]. However, despite suppressive ART, neurodevelopmental delays—which may at times be quite subtle—continue to persist into childhood [9] raising concern for the adolescent years [10].

Data describing developmental trajectories of HEU children is conflicting with some studies reporting cognitive and motor deficits [11], but these may also be attributed to co-varying risks related to parental HIV infection such as poverty, disruption in schooling, and reduced wellbeing [12].

Effective interventions stimulating ECD can have far-reaching positive outcomes, but little is known about the long-term impact of an intervention started at birth in conjunction with early antiretroviral treatment (ART) initiation. The primary aim of this study is to assess neurodevelopmental outcomes of early-treated HIV-infected children receiving an age-appropriate stimulation program and compare them with HIV-infected and HEU children not having received the stimulatory intervention. In addition, associations between neurodevelopmental outcomes, environmental factors, and parental stress will be examined.

## Main text

The study is designed as a non-randomised controlled intervention study.

### Subject selection

Study participants will be recruited from an existing cohort of early-treated HIV-infected and HEU children enrolled onto a clinical trial investigating viral latency and early neonatal provision of anti-retroviral drugs (NCT02431975). Children enrolled and in follow-up in the existing cohort will be offered inclusion into this study, making up the assessment only group. New-born infants will be offered co-enrolment onto the existing study and will make up the group receiving the intervention as well as the assessment. Refusal to participate in one protocol will not jeopardise inclusion onto the other. The trial will be conducted at Rahima Moosa Mother and Child Hospital (RMMCH), Johannesburg, South Africa. The study was approved by the Human Research Ethics Committee of the University of the Witwatersrand (M170653) and registered with the Pan African Clinical Trial Registry (PACTR 201801002967587). Caregiver written informed consent will be obtained.

### Sample size

All children in the existing cohort will be enrolled and assessed using the BSID-III at a single time-point i.e. either at 12, 24 or 36 months of age. 45 children will be enrolled into the intervention group. Hutchings and Potterton, investigating developmental outcomes of HIV-infected and HEU infants [13] reported average cognitive composite scores of 100.31 ± 12.75 for HEU and 75.89 ± 17.69 for HIV-infected infants. Groups of 45 will provide > 90% power to detect a mean cognitive composite score difference of 25 assuming a standard deviation of 17. Hutchings also reported a mean composite language score of 96.28 ± 10.13 and 77.18 ± 16.22 and mean composite motor score of 106.16 ± 10.20 and 79.71 ± 20.91 for HEU and HIV-infected groups respectively. Groups of 45 participants provide > 90% power to detect a difference of 25 in the mean language and motor scores assuming a standard deviation of 16 and 20, respectively. Feasible study enrolment period; number of births per month at RMMCH; and maternal and neonatal HIV prevalence were considered when planning the sample size.

### Inclusion and exclusion criteria

Children less than 36 months enrolled onto the existing cohort trial are eligible for inclusion. Newborn HIV-infected infants initiated on ART whose caregiver provides informed consent will be included. Caregivers unable to comply with follow-up; serious birth defects; uncontrolled maternal psychiatric illness; and inability to provide informed consent will result in study exclusion.

### Study procedures

Trained assessors will conduct the BSID-III on children enrolled from the existing cohort at a single time point. Inter-rater reliability of BSID-III administration will be established. Prematurity will be corrected until 24 months chronological age for a gestational age < 37 completed weeks.

The BSID is a direct assessment test using test kit objects to evoke a response. Five developmental domains are evaluated: cognitive, motor, language, social-emotional and adaptive behavior [14]. The BSID have been normed in South Africa [15].

The intervention group will receive a standardised set of developmentally stimulating toys. At three-monthly intervals, additional items will be provided (Table 1).

**Table 1 Tab1:** Items provided to the intervention group through the first year of life

Child’s age	Items provided
Birth	Baby blanket, washcloth, booties and hat, rattle
3 months	Mirror, small ball, book, squeaky toy
6 months	Ring stacker, large ball
9 months	Wooden blocks, stacking cups, book
12 months	Wooden form board, toy car, plastic doll, picture book, crayons and paper

Caregiver information cards developed in South African as part of a developmental activity programme will be provided three-monthly [16]. The card explains what is expected of a child at certain ages in terms of physical, cognitive, language and socio-emotional development. Play ideas and indications of possible developmental delay are included.

BSID-III will be conducted on the intervention group at 12 months of age. The intervention includes visible components—educational toys and parental information cards—and clinic files of these children will be marked to ensure they receive the intervention. Consequently, neither study participants nor assessors are masked to the intervention assignment. Furthermore, by nature of the timing of the assessment conducted at the 12 month follow-up visit the assessor would be able to deduce that the child received the intervention. Assessors have been trained to complete the assessment regardless of exposure to developmental interventions. Baseline comparability in the HIV-infected infants will be established.

### Study measures

Demographic and health-related variables will be collected from the patient’s files for participants enrolled in the existing cohort. Infant data includes birth history; serial anthropometric data; morbidity data; ART history; concurrent medication; immunisations; feeding history; and laboratory data i.e. HIV viral load, HIV total nucleic acid test, CD4 count, and full blood count (FBC). Maternal data consists of: serial anthropometric measurements; ART history; and laboratory data i.e. HIV viral load, CD4 count, and FBC. Permission for data use has been granted by the database holder and site clinical staff are aware of the aims and logistics of the study.

Composite scores for the three developmental subscales of the BSID-III which are administered with direct child interaction—cognitive, motor, and language—will be recorded [14]. Raw scores are converted to scaled scores which are used to derive the composite score for each subscale.

The household survey and the Parenting Stress Index-Short Form (PSI-SF) will be completed with the child’s caregiver. The household survey is a self-styled questionnaire gathering data about the household in which the child lives. Questions cover the following categories: family structure; number of household members diagnosed with HIV; parental nationality; employment; cigarette and alcohol use; water and sanitation measures; type of housing; exposure to sexual abuse and physical violence; childcare arrangements; and access to electricity and basic electronic household items. The household survey consists of a broad set of variables as ECD is influenced both negatively and positively by a myriad of factors [17–19]. The PSI-SF is the condensed version of a self-reported screening tool used to explore parental stress levels associated with parenting children aged 1 month–12 years [20]. Maternal HIV infection can impact parenting skills which in turn influences the child’s wellbeing, ECD and childhood outcomes [21, 22].

### Data analysis

De-identified data from paper case report forms will be entered into a secure database. Statistical calculations will be performed using SAS version 9.4 (Cary, North Carolina, USA). Anthropometric Z-scores will be calculated using WHO software [23]. P-values will be two-tailed and p-values < 0.05 will be considered statistically significant.

Descriptive statistics will describe the characteristics of the early-treated perinatally HIV-infected children enrolled in the existing cohort in terms of demographics, growth parameters, and HIV-related factors. Composite cognitive, language and motor scores will be described. Continuous variables with normal distribution will be described using means and standard deviation with a 95% confidence interval. Frequency tabulations and percentages will be used to describe categorical variables. “At risk” of developmental delay will be defined as any composite score less than 85, and “delayed” as a score less than 70 [24]. Number of children in these two categories will be explored and associations between patient and disease characteristics investigated using the Chi squared test at 5% level of significance. Mean composite scores will be compared between children assessed at 12, 24 or 36 months of age using ANOVA.

Mean composite scores and number of children “at risk” or “delayed” in each subscale will be compared between early-treated HIV-infected and HEU infants assessed at 12 months of age. T tests will compare demographic, clinical and anthropometrical data between groups. The analysis will be expanded to include the HIV-infected infants having received the ECD intervention. The Chi squared test and Kruskall-Wallis 1-way ANOVA will be used to measure variable difference between groups.

Univariate and multiple regression analyses will be performed to establish associations with poor outcomes on the three subscales i.e. composite scores less than 70 or 85. Variables used to establish associations with poor outcomes will include maternal antenatal and postnatal health-related factors, infant birth data, infant health and HIV-related variables, and data pertaining to socioeconomic status and parental stress. Logistic regression will be conducted on various risk factors for each subscale and a score of ≤ 85 will constitute a poor outcome.

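### Three unranked BSID-III subscales and no named primary contrast, with every test judged at two-tailed 0.05, put the false-positive chance for the programme's effect well above 5%

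*Protocol article*

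**What the plan says.** The Data analysis section sets a single threshold for everything: "P-values will be two-tailed and p-values < 0.05 will be considered statistically significant".

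The outcome has three parts. Study measures lists "Composite scores for the three developmental subscales of the BSID-III which are administered with direct child interaction", namely cognitive, motor and language. Sample size gives a separate power statement for cognitive (25 points, SD 17) and then claims "power to detect a difference of 25 in the mean language and motor scores assuming a standard deviation of 16 and 20, respectively". It does not rank the three.

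The aim in the Introduction is equally broad: "The primary aim of this study is to assess neurodevelopmental outcomes of early-treated HIV-infected children receiving an age-appropriate stimulation program", and to "compare them with HIV-infected and HEU children not having received the stimulatory intervention". That gives two comparators, with neither contrast put first.

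In Data analysis, mean scores and the counts below the two cut-offs (85 for at risk, 70 for delayed) "in each subscale will be compared between early-treated HIV-infected and HEU infants assessed at 12 months of age". The intervention infants are then added to this analysis, using chi-squared and Kruskal-Wallis tests. The same cut-offs return in the regressions for poor outcome, described as "composite scores less than 70 or 85".

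**The concern.** With no primary subscale, form of outcome or contrast, the stated rule treats p<0.05 on any of them alike. A report could lead with whichever subscale or cut-off happened to cross the line, and nothing in the article would mark that choice as made after the fact.

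What is at stake is how a mixed result would be read, for example language significant and cognitive and motor not. The study is non-randomised and its assessors know who received the programme, as the article says. An isolated positive therefore already needs careful reading, and an unranked set of tests weakens it further. Controlling the error rate would not remove those other biases.

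**Working it through.** **Inputs from the article.** Two-tailed alpha 0.05; three subscales; cut-offs 85 and 70; 45 per group; planned difference 25 points; SD 17 (cognitive), 16 (language), 20 (motor).

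**Assumptions not in the article.** Common between-subscale correlation of 0 to 0.7; normal scores rounded to whole points, with mean 76 and SD 17 (close to the cited HIV-infected cognitive figures) or mean 90 and SD 16; t tests for means and uncorrected chi-squared tests for the cut-offs; 45 infants in the non-intervention HIV-infected group at 12 months.

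**1. The plan's own power figure.** The noncentrality is (25/SD) × √(45/2): 6.98 cognitive, 7.41 language, 5.93 motor. The two-sided t test on 88 degrees of freedom gives power of 99.99996%, above 99.99999% and 99.995%. The stated power above 90% is reproduced on all three.

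**2. Three mean scores, one contrast, no effect.** If independent: 1 − 0.95³ = 14.3%. In the programme's favour only: 1 − 0.975³ = 7.3%. Positive correlation lowers both.

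**3. Nine tests, one contrast, no effect.** Independence would give 1 − 0.95⁹ = 37.0%. That is too high, because the two cut-offs are taken from the same score as the mean. Simulation is needed.

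Results from 40,000 null trials per setting, in per cent. Each cell gives mean 76/SD 17, then mean 90/SD 16.

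| Correlation | Any of 3 means | …favouring programme | Any of 9 tests | …favouring programme |
|---|---|---|---|---|
| 0 | 14.0, 14.2 | 7.1, 7.2 | 29.6, 32.8 | 15.5, 17.2 |
| 0.3 | 13.4, 13.4 | 6.8, 6.7 | 29.2, 32.0 | 14.9, 16.4 |
| 0.5 | 12.6, 12.4 | 6.2, 6.2 | 28.0, 30.3 | 14.1, 15.3 |
| 0.7 | 11.0, 10.9 | 5.5, 5.4 | 25.0, 28.3 | 12.6, 14.1 |

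The benchmark is 5% for either direction and 2.5% for the favourable one.

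**4. Three-group reading.** If the tests after the intervention group is added are omnibus tests, nine of them (Kruskal-Wallis and two chi-squared tests per subscale) give 24–30% when all three groups are alike (20,000 simulated trials per setting, same score assumptions).

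**5. Effect of Holm across the three means.** The strictest step is 0.05/3 = 0.0167. In the same simulation the chance of any false positive falls to 3.8–5.0%. Power at 25 points is above 99.999% for cognitive and language and 99.97% for motor.

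The normal approximation to the cognitive difference detectable with 90% power is SD × √(2/45) × (z₁₋α/₂ + 1.282):

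- at 0.05: 17 × 0.2108 × (1.960 + 1.282) = 11.6; exact t calculation 11.7;
- at 0.0167: 17 × 0.2108 × (2.394 + 1.282) = 13.2; exact t calculation 13.4.

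**The case against.** Several objections have force.

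- **Scope.** Multiplicity procedures are often left to an analysis plan or full protocol, and neither is shown. Silence on adjustment is therefore not the point. What remains is what the article itself fixes: a blanket threshold, three unranked power statements and an aim with no leading contrast.
- **A chance positive is likely.** A reader might infer this, but the figures do not support it. A probability above one half requires counting nine tests against each of two comparators as 18 independent tests (1 − 0.95¹⁸ = 60.3%). With realistic dependence those 18 give 42–51%, and the single contrast that matters gives 25–33%.
- **A pairwise grid against two comparators.** This can be inferred from the aim, but it is not the stated test list, which reads most naturally as three-group tests. That reading does not cure the problem. Nine omnibus tests still carry 24–30%, and an omnibus rejection does not show that the programme groups differ.
- **HEU contrasts are not expected to be null.** The planned 25 points is of the size of the reported HEU versus HIV-infected differences, so a significant HEU contrast may well be real. This stands, and it is why the figures here are confined to the two HIV-infected groups.
- **Only half of false positives favour the programme.** True: about 5–7% for three means and 13–17% for nine tests. The nominal rate in that direction is also halved, to 2.5%, so the relative inflation is unchanged.
- **Success on any one subscale.** The article sets a significance threshold, not a success criterion, so it contains no explicit any-of-three rule. The weakness is that it does not exclude one.

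**Conclusion.** The point holds in a limited form. The article judges every test at two-tailed 0.05 while leaving three subscales co-equal and no contrast primary. If the programme has no effect, the comparison of the two HIV-infected groups at 12 months yields at least one p<0.05 in about 11–14% of trials over the three means, and in about a quarter to a third over the nine tests. About half of these would favour the programme.

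The figures rest on assumed correlations of 0 to 0.7, assumed score distributions and 45 infants per group. The article fixes 45 for the intervention group. It does not say how many non-intervention HIV-infected infants will be assessed at 12 months rather than at 24 or 36. The error rates depend little on that number; the detectable differences depend on it directly.

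One further inference should be resisted: that the cognitive composite is the implied primary outcome because the sample size mentions it first. Order of mention is not a ranking, and all three have their own power statement. The defect is worth correcting before results are seen, but it does not undermine the study.

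**What to change.** In Data analysis:

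1. Name the 12-month contrast of intervention versus non-intervention HIV-infected infants on mean composite scores as the primary comparison.
2. Apply Holm across the cognitive, language and motor composites at an overall two-tailed 0.05. Alternatively, the sponsor names one primary subscale in advance and tests the other two in fixed order.
3. Label the cut-off analyses (below 85, below 70) and all contrasts with HEU children as secondary, reported with confidence intervals.
4. Restrict the 0.05 rule to the primary comparison so defined.

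The cost is wording, plus a small loss of sensitivity under Holm. At its strictest step the cognitive difference detectable with 90% power rises from 11.7 to 13.4 points with 45 per group, and power at the planned 25 points stays at or above 99.97% on all three subscales. With one subscale named first, that test keeps the full 0.05 and loses nothing; the price is that the later subscales can be claimed only if those before them succeed.

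### The chi-squared association tests in the HIV-infected existing cohort pool children assessed at 12, 24 or 36 months without stratifying by age, so characteristics that change with age can look linked to delay if delay rates also differ by age.

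*Protocol article*

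**What the plan says.** The Sample size section of the protocol article states that all children in the existing cohort are "assessed using the BSID-III at a single time-point i.e. either at 12, 24 or 36 months of age".

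In Data analysis, the paragraph on this cohort opens: "Descriptive statistics will describe the characteristics of the early-treated perinatally HIV-infected children enrolled in the existing cohort". It names no single age. At risk is then defined as any composite score below 85 and delayed as a score below 70, and the association step follows: "Number of children in these two categories will be explored and associations between patient and disease characteristics investigated using the Chi squared test", at the 5% level. The next sentence is the only place where assessment age is used as a factor: "Mean composite scores will be compared between children assessed at 12, 24 or 36 months of age using ANOVA".

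The following paragraph does restrict by age: it compares HIV-infected with HEU infants at 12 months only.

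A later paragraph plans regressions for poor outcome. The variables will include maternal health factors and "infant birth data, infant health and HIV-related variables, and data pertaining to socioeconomic status and parental stress". Assessment age is not named, and the paragraph does not say which children enter the models.

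**The concern.** A child tested at 36 months has lived up to 24 months longer than one tested at 12 months. In children treated from soon after birth, that child has also been on ART for up to about 24 months longer. Study measures lists ART history, viral load, total nucleic acid, CD4 count and full blood count among the infant data, and several of these can shift with age or treatment time.

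If the proportion scoring below 85 or 70 also differs between the three ages, the pooled two-way table mixes an age effect into the association. A chi-squared test on that table cannot remove it. The trial could then report a disease characteristic as linked to delay when the only driver is the age at testing.

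This is more than a detail left open. The article names an unadjusted test for a mixed-age group, treats age as a possible source of score differences in the next sentence, and does not carry age into the association step.

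**Working it through.** **The plan's own figure.** The only computed design figure is power above 90% with groups of 45 for a 25-point difference. The standard error is SD × √(2/45) = SD × 0.2108. For SD 17, 16 and 20 this gives 3.58, 3.37 and 4.22, and 25 divided by each gives 6.98, 7.41 and 5.93. Power exceeds 99.99% for all three, so the statement reproduces. It has no bearing on this point, and no other figure in the article does.

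**Inputs from the article.** Three assessment ages; one assessment per child; a binary poor outcome; a chi-squared test; two-sided 5%.

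**Assumptions.** The article gives neither the number of HIV-infected children per age nor any rate by age. I assumed 20, 30 or 45 children per age, and rates at 12/24/36 months as in the table. Within each age, the binary characteristic and the outcome are independent, so every significant result is false.

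**How a spurious odds ratio arises.** Average the cell probabilities over three equal age groups. With poor outcome 20/30/40% and the characteristic present in 30/50/70%, the sums over ages are:
- present, poor: 0.06 + 0.15 + 0.28 = 0.49
- present, not poor: 0.24 + 0.35 + 0.42 = 1.01
- absent, poor: 0.14 + 0.15 + 0.12 = 0.41
- absent, not poor: 0.56 + 0.35 + 0.18 = 1.09

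Pooled odds ratio = (0.49 × 1.09)/(1.01 × 0.41) = 1.29. With 15/30/45% and 20/50/80% it is (0.54 × 1.14)/(0.96 × 0.36) = 1.78. The true odds ratio within each age is 1 in both cases.

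**Error rates.** 20,000 simulated data sets per setting. The pooled statistic is N(ad − bc)²/[(a+b)(c+d)(a+c)(b+d)]. The Cochran-Mantel-Haenszel (CMH) statistic is [Σ(aₖ − mₖyₖ/n)]²/Σ[mₖ(n−mₖ)yₖ(n−yₖ)/(n²(n−1))], where n is the number per age, and mₖ and yₖ count children with the characteristic and with a poor outcome at age k. Both are compared with the 5% point of chi-squared on 1 degree of freedom. Entries are pooled / CMH false-positive rates.

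| Poor outcome by age | Characteristic by age | Pooled OR | 20 per age | 30 per age | 45 per age |
|---|---|---|---|---|---|
| 30/30/30% | 20/50/80% | 1.00 | 5.0% / 4.7% | 5.0% / 5.1% | 4.9% / 5.0% |
| 15/30/45% | 50/50/50% | 1.00 | 5.2% / 4.9% | 5.0% / 4.9% | 5.2% / 5.1% |
| 20/30/40% | 30/50/70% | 1.29 | 7.3% / 4.9% | 8.9% / 5.4% | 10.6% / 5.0% |
| 20/30/40% | 20/50/80% | 1.47 | 10.2% / 4.9% | 13.5% / 5.0% | 17.2% / 5.0% |
| 15/30/45% | 30/50/70% | 1.47 | 10.9% / 5.0% | 12.9% / 4.9% | 18.0% / 5.2% |
| 15/30/45% | 20/50/80% | 1.78 | 17.3% / 5.0% | 23.9% / 5.0% | 32.9% / 4.9% |

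The first two rows show that both legs are needed: if either the outcome or the characteristic is flat across ages, nothing is inflated. Where both trend, a larger cohort makes the error worse, because the bias does not shrink.

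**Second model.** Here scores have SD 15 and mean 90 at 12 months, falling by a fixed amount per year, with 20 children per age and a continuous marker split at its median. The chi-squared test rejects in about 9% of runs for 2.5 points and 1 SD of marker shift per year, 15% to 17% for 5 points and 1 SD, and 26% to 27% for 5 points and 2 SD. With no fall in scores there is no inflation. A logistic regression behaves similarly without age (8% to 28% in these settings) and rejects in about 4% to 5% with age group included.

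**The case against.** The strongest reply is that composite scores are built for comparison across ages. Study measures says raw scores are converted to scaled scores and then to composites, and Study procedures says the scale has been normed in South Africa. If that works in this population, outcome rates do not trend with age and the pooled test is sound. This stands in part: it weakens the outcome leg but does not remove it. The plan itself asks the question through the ANOVA, and prematurity is corrected only until 24 months, so preterm children tested at 36 months are scored differently from those tested at 12. The ANOVA could reveal an age trend, but it does not adjust the association tests for one.

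Several stronger readings are tempting and the article does not support them:
- **That the regressions pool ages and leave age out.** Their population is not stated. The paragraph follows one on infants assessed at 12 months, so a 12-month model is as readable, and the variable list is open.
- **That markers are taken at the latest visit.** No time point is given. With pre-ART values the marker leg would largely disappear. Nor does the article say that laboratory results are serial; it uses that word for anthropometric measurements.
- **That a stated aim is compromised.** The Introduction's secondary aim concerns environmental factors and parental stress. HIV markers enter only as analysis variables.
- **That age adjustment rescues time on ART.** In early-treated children the two are nearly collinear, so adjustment leaves little to estimate.

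**Conclusion.** The point holds for the chi-squared step. The article fixes an unstratified test on children assessed at three ages, and a better method is available at almost no cost. The size is conditional. Under the age trends assumed here the 5% error rate becomes about 7% to 33%, with spurious odds ratios of 1.29 to 1.78; without an age trend in outcome it stays about 5%. The rates by age and the numbers per age are assumptions, so this is a range of what could happen and not a forecast that false risk factors will be reported.

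For the regressions the point is only conditional: it applies if they pool ages. The 12-month comparison of HIV-infected with HEU infants, and its extension to the intervention group, are not affected. The tests at issue are exploratory, so this is a worthwhile correction and not a threat to the primary aim.

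**What to change.** In Data analysis:
1. Stratify the tests of at-risk and delayed status against patient and disease characteristics by assessment age (12, 24, 36 months) using Cochran-Mantel-Haenszel, or restrict them to one age.
2. State which children enter the poor-outcome regressions, and include assessment-age group in any model that pools ages.
3. State the time point of each HIV marker and, where the data allow, use one at an age common to all children.
4. Do not report time on ART as an independent risk factor from pooled ages.

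The cost is wording plus two degrees of freedom for age group (three groups minus one) in a regression. Assessment age is known for every child. Restricting to one age would instead cost the children tested at the other two. Item 3 depends on what the files contain, which the article does not settle.

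### The only tests named for the comparison that includes the intervention group are three-group omnibus tests with HEU infants, and a significant result from them does not identify a programme effect

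*Protocol article*

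**What the plan says.** All references are to the Protocol article.

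- **Question.** The Abstract (Methods) asks whether the programme, with ART from birth, "can positively impact neurodevelopmental outcomes at 1 year of age in children infected with HIV".
- **Comparators.** The primary aim in the Introduction is to assess stimulated HIV-infected children and "compare them with HIV-infected and HEU children not having received the stimulatory intervention". It names both comparators.
- **Analysis.** Under Data analysis, mean composite scores and counts of at-risk or delayed children "will be compared between early-treated HIV-infected and HEU infants assessed at 12 months of age". Next, "The analysis will be expanded to include the HIV-infected infants having received the ECD intervention". The tests follow: "The Chi squared test and Kruskall-Wallis 1-way ANOVA will be used to measure variable difference between groups".
- **Significance.** "P-values will be two-tailed and p-values < 0.05 will be considered statistically significant".
- **Size.** Under Sample size, "45 children will be enrolled into the intervention group", and "Groups of 45 will provide > 90% power to detect a mean cognitive composite score difference of 25 assuming a standard deviation of 17". The score differences cited there are between HEU and HIV-infected infants, not between stimulated and unstimulated children.

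The regression analyses in the same section look for factors associated with low scores. Their listed variables do not include intervention group.

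**The concern.** Once the intervention group is added there are three groups: HIV-infected with stimulation, HIV-infected without, and HEU. Kruskal-Wallis and a three-row chi-squared test ask whether any of the three differs from the others. The programme question concerns only the first two.

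The Sample size section itself expects HEU and HIV-infected infants to differ widely. If they do, the omnibus null is false whatever the programme does, and a small p-value says nothing specific about stimulation. Kruskal-Wallis also gives no estimate of the difference in means, which is the quantity used for the sample size. The study is non-randomised and its assessors are unmasked, so a non-specific p-value could easily be misread as benefit.

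**Working it through.** **1. The plan's own power figure.** Inputs from Sample size: 45 per group, difference 25, SD 17 (cognitive), 16 (language), 20 (motor), two-sided 0.05. For the cognitive score the standard error is 17 × √(2/45) = 3.58, so the noncentrality is 25/3.58 = 6.98. With 88 degrees of freedom the power is above 99.9%. The language and motor noncentralities are 25/3.37 = 7.41 and 25/4.22 = 5.93, again with power above 99.9%. The stated figure of more than 90% is reproduced. It describes a gap of the HEU-HIV kind.

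**2. What the omnibus test does when the programme has no effect.** Scores were simulated as normal. Both HIV-infected groups were drawn from one distribution, so the true programme effect is zero. The Kruskal-Wallis statistic is H = 12/[N(N+1)] × Σ(Rⱼ²/nⱼ) − 3(N+1), where Rⱼ is the rank sum of group j. It is referred to chi-squared with 2 degrees of freedom at 0.05. The comparison is a two-sample t-test of the two HIV-infected groups (20,000 trials per scenario).

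Means and SDs cited under Sample size, 45 per group:

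| Scale | HEU | HIV-infected (both groups) | Kruskal-Wallis rejects | Direct contrast rejects |
|---|---|---|---|---|
| Cognitive | 100.31 ± 12.75 | 75.89 ± 17.69 | 100% | 5.3% |
| Language | 96.28 ± 10.13 | 77.18 ± 16.22 | 100% | 4.9% |
| Motor | 106.16 ± 10.20 | 79.71 ± 20.91 | 100% | 5.1% |

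A separate run of 5,000 trials per scale found that the three-group chi-squared test on scores below 85 also rejects in 100% on each scale. The two-group chi-squared test rejects in 4.9% to 5.7%.

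**3. Smaller gaps and fewer controls.** The gap in children treated from birth is not given, so it is varied here as an assumption. Sample size fixes 45 only for the intervention group. Existing-cohort children are each assessed once, at 12, 24 or 36 months, so the number of controls at 12 months is unknown; 20 HEU and 20 unstimulated HIV-infected infants is an assumption. Each cell gives the Kruskal-Wallis rejection rate, first with a common SD of 17 and then with the cited cognitive SDs (12.75 for HEU, 17.69 for HIV-infected).

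| True HEU-HIV gap (assumed) | 45 per group | 45 intervention, 20 HIV-infected, 20 HEU |
|---|---|---|
| 0 points | 5.0% / 5.3% | 5.0% / 4.1% |
| 5 points | 26% / 31% | 15% / 17% |
| 8 points | 60% / 70% | 33% / 38% |
| 10 points | 80% / 89% | 48% / 58% |

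The direct contrast rejected in 4.7% to 5.3% of trials in every one of these scenarios.

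**4. What the direct contrast can detect.** For 80% power the detectable difference is (1.96 + 0.84) × SD × √(1/n₁ + 1/n₂). With 45 and 45 this is about 10.0 points (SD 17), 9.5 (SD 16) and 11.8 (SD 20). With 45 and 20 and SD 17 it is 2.80 × 17 × 0.269 = about 12.8 points.

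**The case against.** Several stronger readings are tempting, and the document does not support them.

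- *The test has an inflated type I error.* It does not. Kruskal-Wallis holds its level for its own null; the zero-gap row shows 4% to 5%. The trouble is that this null is not the programme question.
- *The plan will declare benefit on the omnibus p-value.* Nothing in the article makes that p-value the criterion for benefit.
- *The plan does not intend to compare the two HIV-infected groups.* The Introduction and Conclusion name both comparators, and Study procedures promises a check of baseline comparability among the HIV-infected infants. That comparison is plainly intended; what is lacking is a test aimed at it.
- *The plan ignores means.* Data analysis says mean composite scores will be compared, and it describes normally distributed variables with means, SDs and 95% confidence intervals. A reader would see the group means beside any p-value.
- *The 100% figure applies to this cohort.* It carries over a gap from a cited study. The Introduction says that early ART goes with better outcomes and that HEU data conflict, so the gap here may be smaller.

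Two further defences have weight. The sentence on the tests speaks loosely of variable differences and may also cover baseline characteristics, since it follows a sentence on t-tests of such data. A full protocol or SAP, not shown, may add pairwise contrasts. Neither removes the point. The article does more than leave a detail open: it names the tests for the comparison that includes the intervention group, and they do not isolate the programme. If the sentence were only about baseline variables, the article would name no outcome test for the intervention group, and the same clarification would be needed.

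**Conclusion.** The point holds in a limited form. As written, a significant result from the only tests named once the intervention group is added cannot be attributed to the programme, because HIV status alone can produce it. The size depends on the true HEU-HIV gap and on how many controls are assessed at 12 months: near-certain rejection at the cited gap, about 26% to 31% at an assumed 5 points with 45 per group, and about 15% to 17% with an assumed 45/20/20 split. The direction is the same in every scenario with a non-zero gap. These figures rest on normal scores and identical distributions in the two HIV-infected groups. They are rates of a correct but uninformative rejection, not false-positive rates of an invalid test.

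**What to change.** In Data analysis, state that the programme effect will be judged on the 12-month contrast of HIV-infected infants with versus without stimulation, for each composite score, as a difference in means with a 95% CI from a linear model. Because the groups are not randomised, adjust for infant, maternal and household variables already collected, named in advance and limited to those the programme could not have changed. Adjustment reduces imbalance but cannot remove unmeasured confounding, and the report should say so.

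Report intervention versus HEU as a separate contrast with its own 95% CI, since the primary aim names that comparator too. If the three-group omnibus test is kept, state that its p-value is not evidence of a programme effect.

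The cost is slightly more analysis and a few degrees of freedom spent on covariates, which matters more if few controls are assessed at 12 months. No new data are needed.
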